#### Vaccination Status

As new evidence indicates that the COVID-19 vaccination can possibly influence the outcome of Long-COVID positively, details regarding received vaccinations during the follow-up period will be recorded (all currently available vaccines, date of administration, number of doses). Additionally, if a concomitant influenza vaccination was given, this will be recorded too.

### Parameters Collected Regarding COVID-19 Related ICU Stay

If the patient has been enrolled in CCCC previously, the data collected during their ICU stay regarding demographics, ethnicity, presence of predefined comorbidities, severity of critical illness, clinical course during ICU stay and antiviral/antibiotic medications as outlined below will be available for linkage to the follow-up assessments. If the patient has not been enrolled in CCCC, the above information will be collected by the enrolling study team. We will record information about the following possible variants of concern (VOC) or variants of interest (VOI) identified in the patient upon ICU admission: Alpha-B.1.1.7, identified in UK Sept 2020; Beta-B.1.351, identified in South Africa May 2020; Gamma-P.1, identified in Brazil Nov 2020; Delta-B.1.617.2, identified in India Oct 2020; Epsilon-B.1.427/B.1.429, identified in USA Mar 202; Zeta-P.2, identified in Brazil Apr 2020; Eta-B.1.525, identified in Multiple Countries Dec 2020; Theta-P.3, identified in Philippines Jan 2021; Iota-B.1.526, identified in USA Nov 2020; Kappa-B.1.617.1, identified in India Oct 2020; Lambda-C.37, identified in Peru Dec 2020. Detailed information about medical comorbidities, including pre-existing immunosuppression, malnutrition and dementia will be collected. Relevant medication pre-ICU admission will be also recorded, especially angiotensin-converting enzyme inhibitors and/or angiotensin II receptor blockers, non-steroidal anti-inflammatory drugs, corticosteroids or other immunosuppressant drugs, antibiotics and/or antivirals. The last full blood count, biochemistry panel and arterial blood gas analysis while on ICU will be transferred into the electronic database. In terms of supportive treatment, we will record oxygen therapy, non-invasive and invasive ventilation, prone positioning, administration of inhaled nitric oxide, tracheostomy, extracorporeal membrane oxygenation support, cardiac-assist devices and renal replacement therapy as well as the duration in days for every intervention. Collected data regarding pharmacological treatment includes inotropic and vasoactive agents, antiviral or COVID-19 targeted treatment [f.e. ribavirin, lopinavir/ritonavir, remdesivir, interferon alpha and/or beta, (OH-) chloroquine], antibiotic and antifungal agents, corticosteroids and anticoagulation (all in detail regarding preparation, dose, route of administration and duration). In addition, any of the following complications during the ICU stay will be recorded: viral pneumonia/pneumonitis, bacterial pneumonia, acute respiratory syndrome, pneumothorax, pleural effusion, cryptogenic organizing pneumonia, bronchiolitis, cardiac arrest, myocardial infarction, myocarditis/pericarditis, endocarditis, cardiomyopathy, congestive heart failure, seizure, stroke/cerebrovascular event, meningitis/encephalitis, bacteremia, coagulation disorder, DIC, pulmonary embolism, deep vein thrombosis, anemia, rhabdomyolysis, acute renal failure, gastrointestinal hemorrhage, pancreatitis, liver dysfunction, hypo- and hyperglycemia. If a chest x-ray, echocardiography and/or CT thorax was performed while the patient was on ICU, the date of the exam and the detailed results will be recorded. The detailed AFTERCOR case report form can be found at the official AFTERCOR website (https://www.aftercorstudy.com).

### Data Management and Confidentiality

The case report form (CRF) will be available as a paper and electronic CRF (eCRF) for data collection. All documents will be stored securely to maintain confidential conditions. The site Principal Investigator is responsible for securely locking away hard copy documentation and ensuring electronic information is password protected. Access to secure files will only be granted to selected study personnel, this includes access to the online database (REDCap, hosted by the University of Queensland). All data will be cleaned at regular intervals to ensure accuracy and maintain high data quality. On all trial-specific documents, other than the signed consent form, the participant will be referred to by a unique trial-specific patient identifier code, including the electronic database. The electronic database has been developed as a web-based tool and can be accessed online, all entered data is completely de-identified.

### Sample Size Calculation

This is an observational study that will examine multiple research questions. We aim for enrolment of at least 1,000 patients: this sample size will provide good power to detect differences between groups, for example it gives a 90% power to detect a standardized difference of 0.15 between two equally sized groups (using a two-sided alpha of 0.05).

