## Limitations

As this is a long study with multiple and extensive follow-up assessments, a high-drop-out rate of patients is expected. The statistical assumptions will be corrected for this potential confounder of results.

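### The stated 90% power for a 0.15 SD difference does not follow from 1,000 patients in two equal groups; the stated inputs give about 66%, and less after drop-out

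*Protocol article*

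**What the plan says.** The Sample Size Calculation section of the protocol article describes an observational study with several research questions. It then gives the target, "We aim for enrolment of at least 1,000 patients", and says that this number provides good power for comparisons between groups. The one worked illustration is that "it gives a 90% power to detect a standardized difference of 0.15 between two equally sized groups", "using a two-sided alpha of 0.05".

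The section names no endpoint, visit or grouping for this comparison. It mentions no repeated measures, covariate adjustment or allowance for loss to follow-up. The Limitations section says that "a high-drop-out rate of patients is expected" and gives no rate.

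**The concern.** Every input to a two-group power calculation stands in that one passage: total number, allocation, effect size, alpha and sidedness. The stated power can therefore be checked directly, and 90% looks too high for 500 against 500 at 0.15 SD.

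The figure is the only number offered in support of the 1,000-patient target. If it is too high, a comparison that finds no difference may later be read as good evidence against an effect of 0.15 SD when the study had a substantial chance of missing one. Drop-out makes this worse at the later visits, because the calculation counts patients enrolled and not patients analysed.

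**Working it through.** **Inputs, all from the Sample Size Calculation section**
- Total N = 1,000, in two equal groups, so n = 500 per group.
- Standardized difference d = 0.15 (SD = 1).
- Two-sided alpha 0.05, so the critical value is 1.960.
- Stated power 90%, for which the normal quantile is 1.2816.

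**1. Power from the stated inputs**

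Power ≈ Φ(d·√(n/2) − 1.960)

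d·√(n/2) = 0.15 × √250 = 2.372

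Power ≈ Φ(2.372 − 1.960) = Φ(0.412) = 0.660

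The noncentral t calculation gives 0.659. The stated 90% is not reproduced; the gap is 24 percentage points.

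**2. Number needed for 90% power at d = 0.15**

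n per group = 2 × ((1.960 + 1.2816)/0.15)² = 934, so 1,868 in total.

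**3. Difference detectable with 1,000 in total**

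- 90% power: (1.960 + 1.2816) × √(2/500) = 3.2415 × 0.0632 = 0.205 SD.
- 80% power: 0.177 SD by the same formula.

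**4. Other readings that might explain 90%**

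| Reading | Power at d = 0.15 | Fits the text? |
|---|---|---|
| 500 per group, two-sided | 66% | Yes |
| 500 per group, one-sided 0.05 | 77% | No: the text says two-sided |
| 1,000 per group, two-sided | 92% | No: 1,000 is the enrolment total |
| One-sample or paired test, n = 500 | 92% | No: the text compares two groups |

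Using the total as the per-group size, or a one-sample formula with 500, comes close to 90%. Either could be the source of the slip, but the document does not show its calculation, so this is only an inference.

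**5. Effect of drop-out**

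The documents give no rate. The rates below are assumptions chosen to show a range. The formulas are those of steps 1 and 3, with the two groups kept equal.

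| Assumed loss | Analysed | Power at d = 0.15 | Detectable difference, 90% power |
|---|---|---|---|
| 0% | 1,000 | 66% | 0.205 SD |
| 10% | 900 | 61% | 0.216 SD |
| 20% | 800 | 56% | 0.229 SD |
| 30% | 700 | 51% | 0.245 SD |
| 40% | 600 | 45% | 0.265 SD |
| 50% | 500 | 39% | 0.290 SD |

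**6. Unequal groups**

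The stated figure is conditional on equal groups, so this step does not bear on whether it is right. It shows that equal groups are the best case. With 300 against 700, 0.15 × √(300 × 700/1,000) = 2.174 and power is Φ(2.174 − 1.960), about 58%.

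**The case against.** The strongest reply accepts the arithmetic and disputes its weight.

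- **It is only an illustration.** The figure is introduced as an example, in an observational study with a descriptive primary aim. The planned trajectories, latent classes, regressions and survival models do not depend on it, and 1,000 is a minimum. This stands as a description: it is not a primary-endpoint calculation. But an illustrative power must still be true, and the 90% is attached to the stated sample size, not to some larger number that might be reached.
- **A more efficient analysis could reach 90%.** With 500 per group, the residual variance would have to fall to 500 × 0.15²/(2 × 3.2415²) = 0.535 of the raw variance. Adjustment for a covariate correlated about 0.7 with the outcome would give 91% power. Averaging five visits would give 86% at a within-patient correlation of 0.5 and 95% at 0.3. The sample size section states no such assumption and describes a plain two-group difference.
- **Drop-out is dealt with elsewhere.** Statistical Considerations plans to describe drop-out and its predictors, with multiple imputation as a possible sensitivity analysis. Limitations promises an unspecified correction. None of this restores lost power. It is fair, however, that the size of the drop-out effect rests on rates the documents do not give, and that a full protocol may hold a retention allowance.
- **No threshold is attached to 0.15.** The article does not call it a clinically important difference, so how null results will be read is a judgement. That limits the consequence and leaves the error as it is.

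**Conclusion.** The concern holds: the statement is wrong as written. On its own inputs the power is about 66%, so the chance of missing a 0.15 SD difference is about 34%, not the implied 10%. The 90% figure belongs to a difference of about 0.205 SD with 1,000 analysed, or to 1,868 analysed patients at 0.15 SD.

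This rests on a two-sample comparison of means with equal groups, full retention and no variance reduction, which is what the section describes. The further loss from drop-out is certain in direction. Its size is illustrative: about 51% power if 30% of patients are lost. No outside document could make the stated figure agree with its stated inputs.

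**What to change.** Replace the power sentence in the Sample Size Calculation section. Suggested wording: *With 1,000 analysed patients in two groups of equal size and a two-sided alpha of 0.05, the study has 90% power for a standardized difference of about 0.205, and 66% power for 0.15.* Add the detectable difference at the retention the sponsor assumes for the later visits, with that assumption stated; at 70% retention it is about 0.245 SD.

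This costs one or two sentences and a less favourable figure. It changes nothing in enrolment, procedures or analysis.

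If the sponsor does want 90% power at 0.15 SD, wording alone will not do. The total must then be 1,868 analysed patients, which means enrolling 1,868/0.8 = 2,335 at an assumed 20% loss, or 1,868/0.7 = 2,669 at an assumed 30% loss. If the 90% relied on covariate adjustment or repeated measures, the section should state that analysis and the correlation assumed.

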### Statistical Considerations

Summary statistics will be used to describe the sample characteristics at ICU discharge and plots to summarize outcomes over time for both individual patients and averages by groups. Patient trajectories will be plotted over time following discharge to examine patterns in recovery for the key variables of quality of life and lung health. Mean trajectories will be used to summarize the typical trajectory. Latent class analysis will be used to determine whether there are distinct groups of patients in terms of recovery, e.g., fast and slow recovery groups, and whether these groups have particular clinical characteristics. Multivariable regression analyses will be used to examine associations between baseline characteristics and severity variables upon admission and discharge in the ICU, and how these impact outcomes at 3, 6, 12, 18, and 24 months after ICU discharge. The residuals of the models will be checked for multi-modality, skew and outliers. Models will also be checked for collinearity and influential values. Participant drop-out rates will be displayed over time and we will examine whether patient characteristics at baseline predict drop-out. Item-missing data will be summarized, and we may use multiple imputation methods as a sensitivity analysis to compensate for missing data. Long-term survival will be plotted using a Kaplan–Meier plot with censoring for patients lost to follow-up. A multivariable survival model will be used to examine which variables predict survival. We will use the lasso to select the important subset of predictors from a larger set. All analysis will be performed with R (R Foundation for Statistical Computing, Vienna, Austria).

The results of this study will be reported as according to the STROBE guidelines (29).

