## Discussion

This study aims to provide a comprehensive understanding of the long-term impact of COVID-19 in patients who have been admitted to ICU. The primary outcome of the study is to extensively characterize physical, mental and psychosocial consequences post ICU discharge. Secondary outcomes include long-term health and social-economic cost of COVID-19, risks for medical sequelae and long-term survival.

The emerging data and evidence suggest that a significant proportion of critically ill COVID-19 patients will present persistent debilitating symptoms, organ dysfunctions and compromised quality of life post-hospital discharge (4, 6, 12). Results obtained from this study will assist clinicians and healthcare providers to better identify high risk patients who are recovering from COVID-19, then to target interventions that improve their post-COVID-19 quality of life, facilitating a quicker return to productive life. Better understanding of the long-term impact of COVID-19 through data collected in this study will help and inform governments and policy-makers to better allocate resources.

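### Visit means and latent recovery classes are not linked to death before 24 months, so selective mortality can make average scores drift toward better health with no patient improving

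*Protocol article*

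**What the plan says.** The Statistical Considerations section of the protocol article sets out three analyses of recovery.

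- Trajectories: "Mean trajectories will be used to summarize the typical trajectory". The key variables named there are quality of life and lung health.
- Classes: "Latent class analysis will be used to determine whether there are distinct groups of patients in terms of recovery". The examples given are fast and slow recovery.
- Regressions relating baseline and severity variables to outcome, and "how these impact outcomes at 3, 6, 12, 18, and 24 months after ICU discharge".

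Death is treated in the same section, but on its own: a Kaplan-Meier plot that censors patients who are lost, and then "A multivariable survival model will be used to examine which variables predict survival". The Discussion ranks survival among the secondary outcomes: "Secondary outcomes include long-term health and social-economic cost of COVID-19, risks for medical sequelae and long-term survival".

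On incomplete data, Statistical Considerations plans to display drop-out, to look for its baseline predictors, and possibly to use multiple imputation as a sensitivity analysis, in a sentence about missing items. The Limitations section expects much drop-out and promises a correction without describing it. Outside the survival analysis, death and drop-out are not told apart.

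**The concern.** The plan expects deaths within the window over which it averages scores; otherwise it would not list survival as an outcome. A mean over whoever has a score at 24 months describes a different group from the mean at 3 months. If those who died had the lower scores, the later mean is higher for that reason alone, and a reader would see recovery.

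Death also differs in kind from drop-out. A patient who is lost still has a quality of life that was not observed; a patient who has died has none. A correction for drop-out that did not separate the two would supply scores for people who are dead.

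The stake is the study's stated purpose. The Strengths and Limitations section hopes to identify which survivors need closer follow-up. A class that declines and then dies is central to that aim, and the classes as described carry no mortality.

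**Working it through.** **1. The plan's yardstick.** The only effect size in the article is in Sample Size Calculation: "We aim for enrolment of at least 1,000 patients", and "it gives a 90% power to detect a standardized difference of 0.15 between two equally sized groups" ("using a two-sided alpha of 0.05"). With 500 per group, power = Φ(0.15 × √(500/2) − 1.960) = Φ(0.412) = 66%, so the stated 90% is not reproduced. At 90% power the detectable difference is (1.960 + 1.282) × √(2/500) = 0.205 SD. That is a separate matter. Here 0.15 SD serves only as the difference the plan treats as worth detecting.

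**2. Inputs for the drift.**
- From the documents: 1,000 patients; last visit at 24 months.
- Assumed, because the documents give no figure: share p of patients dying between months 3 and 24, taken as 3%, 5%, 10% and 15%; hazard of death multiplied by 2 for each SD lower score (range 1.5 to 2.5); no individual change after month 3; no other loss to follow-up.

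**3. Formula.** With score z ~ N(0,1) and survival to month 24 equal to exp(−λ × HR^(−z)), λ is chosen to give p deaths overall. If d is the gap in SD between the mean score of survivors and of those who die, then

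mean among survivors − mean of the whole cohort = p × d.

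The standard error of the survivors' mean is s / √(1000(1 − p)), where s is the SD among survivors.

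**4. Results at a hazard ratio of 2** (solved by numerical integration).

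| Deaths p | Gap d (SD) | Drift p × d (SD) | s | Standard error | Drift / SE |
|---|---|---|---|---|---|
| 3% | 0.697 | 0.021 | 0.993 | 0.0319 | 0.7 |
| 5% | 0.700 | 0.035 | 0.988 | 0.0321 | 1.1 |
| 10% | 0.708 | 0.071 | 0.977 | 0.0326 | 2.2 |
| 15% | 0.718 | 0.108 | 0.965 | 0.0331 | 3.3 |

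**5. Sensitivity to the hazard ratio (1.5 to 2.5).** The drift is 0.01 to 0.03 SD at 3% deaths (below one standard error throughout), 0.04 to 0.09 SD at 10%, and 0.065 to 0.137 SD at 15%. At a hazard ratio of 2 it reaches about 0.15 SD only at 20% deaths. Drop-out would enlarge the standard errors, so the last column of the table is an upper figure for these inputs.

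**6. What a class without mortality leaves out.** At 10% deaths and a hazard ratio of 2, 19.5% of patients in the lowest quartile at month 3 have died by month 24, about twice the overall rate.

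**7. Per-visit regressions.** With a correlation of −0.4 between score and a severity covariate, the slope among survivors relative to the whole cohort is 0.98, 0.96 and 0.94 at 5%, 10% and 15% deaths: an attenuation of 2% to 6%.

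**8. Which measures.** Table 1 schedules SF-36, SGRQ, PHQ-9 and MoCA at all five visits with no stopping rule, so the direction above applies to them. Under Pulmonary Assessment, lung function, blood gas, chest x-ray and walk test are not repeated once normal. Recovered patients therefore also leave the later means of those measures, which pulls them toward worse health.

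**The case against.** The strongest reply is that the article is silent rather than wrong. It gives about one sentence per method, and how death enters a longitudinal model is commonly left to an analysis plan. Means among those alive are a legitimate target in a cohort of survivors, individual trajectories are to be plotted beside the averages, and deaths are not hidden, since survival has its own analysis. The size rests wholly on assumed inputs, and at a hazard ratio of 2 with up to 15% deaths it stays below 0.15 SD.

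Most of this stands, and it limits the point. What remains is that the article does describe its handling of incomplete follow-up, separates death from loss in the survival analysis, and does not do so for the main summaries. It also calls the mean trajectory typical without saying of whom.

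Several stronger readings are tempting, and the documents do not support them:

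- *Patients who die have no score and fall in no class.* A patient who dies at month 8 has 3- and 6-month scores and can be assigned a class from them. Only a patient who dies before the first visit has none.
- *The poor-recovery class shrinks over time.* The classes are whole recovery patterns, so membership is fixed per patient.
- *The plan imputes scores for the dead.* Imputation is optional, a sensitivity analysis, and tied to missing items. The risk lies in the undescribed correction promised under Limitations.
- *Severity associations are seriously weakened.* The attenuation is 2% to 6% under the assumptions above.

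**Conclusion.** The point holds in a limited form. If visit means are taken over observed scores, selective death of low scorers moves the means of SF-36, SGRQ, PHQ-9 and MoCA toward better health with no patient improving. At an assumed hazard ratio of 2 and 3% to 15% deaths, the drift is about 0.02 to 0.11 SD. It may be negligible if few patients die after month 3, and it exceeds two standard errors of the mean at 10% deaths or more. Mortality, hazard ratio and absence of individual change are all assumptions.

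A reader might infer that all reported recovery, including lung recovery, would be overstated. That does not follow: for the tests that stop once normal, the net direction cannot be told from the documents. The latent classes remain usable, but as described they say nothing about who died. The change is worth making because it is nearly free and removes an ambiguity from the main summaries.

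**What to change.** Amend Statistical Considerations as follows.

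1. Label visit means as *among patients alive at the visit*. Show the percentage dead at each visit, separately from drop-out. Base statements about recovery on within-patient change, not on differences between visit means.
2. Report mortality by latent class. Add a joint latent class model of score and time to death as a sensitivity analysis.
3. State, here and under Limitations, that any imputation or drop-out correction applies only to patients alive at the visit.

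The cost is a few sentences and modest extra programming in R, with no new data, visits or patients. Joint latent class models take longer to fit, and average recovery may look slightly less favourable.

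### The Limitations section promises a correction for expected high drop-out that the analysis text does not contain, leaving late-visit estimates open to selection bias in either direction

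*Protocol article*

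**What the plan says.** Limitations states that "a high-drop-out rate of patients is expected" and follows with "The statistical assumptions will be corrected for this potential confounder of results". It names no method and points to no other section.

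Statistical Considerations deals with drop-out and missing data in these ways:

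- Drop-out is plotted visit by visit, and its causes are explored only as far as this: "we will examine whether patient characteristics at baseline predict drop-out".
- In the survival analysis, patients lost to follow-up are censored.
- For gaps in the recorded data, the whole provision is: "Item-missing data will be summarized, and we may use multiple imputation methods as a sensitivity analysis to compensate for missing data".

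The same section summarises recovery by individual and mean trajectories for quality of life and lung health, by latent classes, and by multivariable regressions of outcomes at 3, 6, 12, 18 and 24 months.

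Two other places matter. Sample Size Calculation says "We aim for enrolment of at least 1,000 patients" and makes no allowance for drop-out. Pulmonary Assessment says that lung function tests, blood gases, chest x-ray and the walking test are not repeated at later visits once a result is normal for the patient.

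**The concern.** A reader of Limitations would expect the analysis to contain some adjustment for drop-out. In Statistical Considerations drop-out is only described. The one technique that could adjust for anything, multiple imputation, is optional, is introduced for item-missing data, and is confined to a sensitivity analysis.

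The late visits are at stake. Two-year follow-up is listed first among the study's strengths, and late visits carry the most accumulated loss. If attendance depends on how the patient has been doing, an apparent change in the mean between 3 and 24 months can be partly a change in who is measured. Relating drop-out to baseline characteristics would not detect this where the driver is the patient's recent health. For lung tests a second mechanism is built into the schedule: recovered patients leave the measured set by design.

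**Working it through.** **1. Can any section supply the promised correction?**

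- Display of drop-out and its baseline predictors: descriptive, and changes no estimate.
- Multiple imputation: optional, introduced for item-missing data, sensitivity analysis only.
- Censoring: applies to survival, not to scores or organ measures.
- Sample size: if the corrected assumptions were meant to be those of the sample size, that section has no allowance either.

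Nothing in the article delivers what Limitations announces.

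**2. The plan's own yardstick.** The only effect size given is in Sample Size Calculation: "it gives a 90% power to detect a standardized difference of 0.15 between two equally sized groups", "using a two-sided alpha of 0.05". With 500 per group, power = Φ(0.15 × √(500/2) − 1.960) = Φ(2.372 − 1.960) = Φ(0.412) = 66.0%, so the 90% is not reproduced. With 1,000 per group it is Φ(3.354 − 1.960) = 91.8%. That is a separate matter. Here 0.15 SD serves only as a measure of what the study regards as worth detecting.

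**3. Size of a selection bias.** Let d be the share lost by a visit and g the gap, in SD, between stayers and leavers at that visit. The full mean is (1 − d) × stayers + d × leavers, so observed mean minus full mean = d × g. The article gives neither d nor g; both are assumed.

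| d | g = 0 | g = 0.2 | g = 0.5 |
|---|---|---|---|
| 0.30 | 0 | 0.06 | 0.15 |
| 0.50 | 0 | 0.10 | 0.25 |

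**4. Check by simulation.** Assumptions: 200,000 patients, five visits, scores with SD 1, within-patient correlation 0.6, and logistic drop-out on the previous score with log-odds ±0.5 per SD. The bias is that of the mean of those still observed at visit five.

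| Who leaves | Lost by visit 5 | Bias (SD) |
|---|---|---|
| lower scores | 29% | +0.09 |
| lower scores | 42% | +0.14 |
| lower scores | 50% | +0.18 |
| unrelated to score | 40% | 0.00 |
| higher scores | 42% | −0.15 |

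Size and sign both depend on who leaves.

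**5. Lung tests.** Under Pulmonary Assessment, a patient with a normal result is not retested. Those still tested later are the unrecovered, so g is negative and the observed mean is too unfavourable unless stopped-because-normal is handled explicitly. The dagger footnote to Table 1, read literally, says instead that tests are repeated upon normalisation; the two places need reconciling.

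**6. Would one model over all visits help?** Assumed set-up: 1,000 patients, five visits, random intercept SD 7, slope SD 1.5 per visit, residual SD 5, severity effect −2 per SD, and drop-out log-odds rising 0.06 per point lower on the last score (odds ratio e^0.6 = 1.8 per 10 points). About 67% are retained. With slopes counted from the first visit, the SD at 24 months is √(7² + (4 × 1.5)² + 5² + 2²) = √114 = 10.7. Across runs with different visit means and centring:

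- Mean of those observed at 24 months: 46.4 to 46.5 against a true 45.0, which is 1.4/10.7 = 0.13 SD to 1.5/10.7 = 0.14 SD.
- Mixed model over all visits: 44.8 to 45.0.
- Severity slope from the 24-month regression alone: −1.83 to −1.93 against −2.00. The largest shortfall, 0.17, is less than half of one study's standard error of about 0.39.

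**The case against.** The strongest reply is that the article never says its main analysis uses only those who attend. A longitudinal mixed model fits the wording on multivariable regression as well as separate regressions at each visit do, and latent class models of trajectories commonly use every observed visit. An article condenses a fuller plan, and random effects for patients or centres, or the covariates of a drop-out model, are normally left to that plan. Limitations also speaks of correcting assumptions, which is vaguer than promising corrected estimates.

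Much of this stands. A reader might infer that the main results are available-case results; the text leaves the model open. A reader might also infer that they are biased toward healthier survivors. The documents do not say who drops out, recovered patients may also stop attending, and the lung-test rule pushes the other way. Nor can one say that death is merged with drop-out throughout, since the survival analysis distinguishes death from loss. The absence of centre effects is analysis-plan detail.

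The simulations are illustrative, and the mixed model in step 6 succeeds partly by construction: drop-out there depends only on observed scores, and the fitted model matches the one that generated the data.

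What survives is the conflict within the article. Statistical Considerations does not leave drop-out and missing data to another document. It assigns them a role, and that role cannot deliver what Limitations announces.

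**Conclusion.** The point holds as a mismatch between Limitations and Statistical Considerations, with a real but unquantified risk of selection bias at late visits. For quality of life the bias is plausibly favourable if sicker patients leave; for lung tests stopped once normal it is plausibly unfavourable. With assumed losses of 30 to 50% and leavers 0.2 to 0.5 SD worse, the shift in the mean is 0.06 to 0.25 SD, a range that contains the study's own 0.15 SD. It is nil if drop-out is unrelated to outcome, and it reverses if better patients leave.

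A stronger claim, that associations with severity are materially weakened, is not supported: the attenuation in step 6 is small against sampling error. The change should be made before analysis.

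**What to change.** In Statistical Considerations:

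- Make the primary analysis of repeated scores a likelihood-based mixed model using all observed visits, with visit-by-predictor terms and patient random effects, and derive the mean trajectories from it.
- Include prior outcome values, not only baseline characteristics, in the drop-out model and in any imputation or weighting. Weighting alone cannot recover stopped lung tests, because under the stopping rule nobody with a normal result is retested.
- Report at each visit the numbers who died, were alive but not assessed, had the test stopped because normal, and were assessed. Do not impute scores beyond death.
- Add a delta-adjusted missing-not-at-random sensitivity analysis.

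In Limitations, replace the general promise with a reference to this method.

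The cost is wording and modest extra programming in R, with no new data collection. The downside is that the primary model relies on data being missing at random, which is why the delta-adjusted analysis is needed.
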